### Evaluator independence

An independent team from Virginia Tech’s Center for Public Health Practice and Research, separate from the academic team and community research teams, is responsible for the evaluation of the research project, including randomizing participants, collecting evaluation survey data, and assessing results. The evaluation team consists of a Principal Investigator trained in public health program evaluation, a project associate, and two graduate research assistants. All authors contributed to the evaluation plan, including team members responsible for planning and implementing the program. All team members will review and interpret the findings.

## Discussion

With the increasing popularity of community engaged research, there is an urgent need for data on the effectiveness of different engagement methods to help researchers and community partners make decisions about which methods are best suited to their needs. This research protocol describes a study comparing the effectiveness of two community engagement methods, the SEED Method and the Delphi method, and a control intervention. Participants in three rural counties will create local strategies for addressing opioid misuse and prioritize those strategies for use in community action planning. Community members participating in the study represent a range of relevant stakeholders. We will assess changes in the self-rated civic engagement of participants and compare the number and types of strategies created and prioritized using the three methods evaluated. This protocol describes a group randomized controlled trial to evaluate the effectiveness of these methods on increasing the civic engagement of participants and on the number, quality, and type of strategies created. Given the design of the study, we will be able to compare the SEED Method to the Delphi Method and compare both of these methods to the control group. We will also be able to explore how effects differed depending on participant role (community research team member, intervention/control group participant, and focus group participant).

The strengths of this protocol include replicating the implementation of the SEED Method, which was previously used in a rural Virginia county and a large midwestern city, to develop community strategies for reducing opioid misuse. Furthermore, we will use a rigorous randomized design with data collected at three time points. While the protocol was developed collaboratively with the previous developers of the SEED Method, an independent evaluation team will collect and analyze the data. Limitations could include the small sample size and the use of a relatively new outcome measure (the Mobilization Scale). Further limitations could result from the ability to recruit and retain the target number of participants in the rural communities. While we have specified recruitment targets and project activities, this is community-led research, and some decision-making will take place during implementation by community teams, which is considered a normal part of the process.

In addition to comparing community engagement methods, this project will highlight the ways in which community-based, participatory processes can contribute to the development of local strategies for addressing the causes and consequences of opioid misuse. Community input and collaboration are important to identify local needs and resources, communicate local values, find opportunities to build awareness, and develop programs and policies for prevention, treatment, and related services. The proposed strategies will be valuable to local governments seeking ways to identify local priorities to help allocate opioid abatement funds. Understanding the impact of the SEED and Delphi methods on strategy development may also help decision makers weigh potential community engagement options as they seek community input on opioid abatement priorities or other community needs.

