### Interventions

Two counties will use the SEED Method and one county will use a modified Delphi method. We were originally funded to implement the SEED Method in three counties but decided to implement the Delphi method in one county for comparative and logistical reasons.

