### Recruitment

Recruitment will occur through a combination of outreach strategies, including personal contacts, flyers and messages sent to partner organizations to be shared with potential participants, social media postings or advertisements, and advertisements in local media. The outreach materials will provide contact information for the study coordinator. The study coordinator will review eligibility criteria with potential participants and confirm eligibility for a specific stakeholder group within the relevant site. Once deemed eligible, the research coordinator will obtain informed consent. The target is 48 participants per county (144 total) divided as follows: 24 in the intervention group (For the SEED Method they are further divided into three stakeholder Topic groups) and 24 in the control group (composed of an equal number of stakeholders from each group). These are our target numbers, but flexibility will be allowed which may result in some stakeholder groups being larger or smaller than the target based on the community research teams’ ability to recruit.

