### Randomization

A member of the evaluation team will randomize when there are eight consented participants in a specific group. Each of the eight consented participants will be assigned a unique number from one to eight. Using the “Sequence Generator” from random.org, participants will be randomized to an intervention or control group. This process will be repeated until each intervention group/control group has the target number of participants.

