### Sample size and power analysis

**Table 3 Tab3:** Number of planned participants by site and intervention type

	Site 1 (SEED Method)	Site 2 (SEED Method)	Site 3 (Delphi method)
**Intervention**	24 (3 groups of 8)	24 (3 groups of 8)	24 (1 group, with number of specific stakeholder groups TBD)
**Control**	24	24	24

The power analysis is calculated based on the sample sizes of the intervention and control group participants only. A target number of 48 participants per community will be recruited and randomized to the intervention or control condition (24 per condition) (Table 3). Minimal detectable differences between the variables of primary interest were estimated with this sample size, setting the alpha error at 0.05 and the beta error at 0.20, adjusting for the estimated ICC and the usual population variances based on cited research (Table 4). Based on these analyses, the anticipated sample size will have an 80% probability of detecting treatment differences in the primary outcomes if the true differences are in the range of the minimum detectable differences. These scores were calculated based on the standard deviations reported by Kasmel and Tanggaard [38].

**Table 4 Tab4:** Minimum detectable differences (MDD) in primary outcome variables

Minimum Detectable Difference (MDD) and Percent Minimum Detectible Difference (%MDD)			
Estimated *n* = 144	$$\:\underset{\_}{x}$$ ^*^	SD^*^	MDD (%MDD)
Mobilization Scale (Total)	1.87	0.37	0.12 (6.5)
Participation Subscale	1.70	0.56	0.18 (10.9)
Motivation Subscale	1.83	0.56	0.18 (10.1)

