### Data analysis

For the survey data, descriptive univariate analyses will be conducted on all study variables. The data will be checked for outliers, violations of normality and missing data. Predictors of drop-out and nonresponse will be explored to better understand any discernible systematic processes in play, taking advantage of the data collected until the last time point and demographic variables. If the missing data are found to be random and ignorable, multiple imputations will be used to address missing data [42]; otherwise, an intent-to-treat approach that makes full use of available data in determining intervention effects will be used for all analyses.

Scale scores will be calculated for all outcomes. The first step will be to calculate the intraclass correlation coefficient (ICC) to determine what percentage of the variance in the dependent variable is attributed to being from the same community. If the ICC at the community level is negligible, the community will not be used in the nested structure, and robust standard errors will be estimated to correct for the nested data structure. For primary and secondary outcomes, a two-level clustered longitudinal model with growth trajectories (change from Year 1 to Years 2 and 3) will be assessed at level 1 for each participant; variation in growth parameters among participants depending on the treatment status nested within location will be captured in the level 2 model. STATA will be used to estimate these two-level models. Covariates at different levels will be included at the two levels as predictors to isolate the effects on treatment outcomes. The two-level longitudinal model in STATA can be utilized for continuous as well as categorical and binary outcomes with minor changes in the interpretation of coefficients.

Data collected during the focus groups is for the purpose of including additional perspectives to the community research team members and Topic group members. Analysis of the data will focus on identifying themes from the information shared in the focus groups and summarizing them for discussion.

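### The Discussion calls this a group randomized trial although individuals are randomised within each county, and the analysis text does not make clear how intervention versus control relates to county

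*Protocol article*

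**What the plan says.** All references are to the protocol article.

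- **Discussion:** "This protocol describes a group randomized controlled trial to evaluate the effectiveness of these methods on increasing the civic engagement of participants".
- **Randomization:** once eight people have consented in a specific group, "Each of the eight consented participants will be assigned a unique number from one to eight", and "participants will be randomized to an intervention or control group". The Abstract (Methods) likewise has the evaluation team randomising participants.
- **Sample size and power analysis:** "A target number of 48 participants per community will be recruited and randomized to the intervention or control condition (24 per condition". Table 3 shows 24 intervention and 24 control participants at each of the three sites.
- **Interventions:** "Two counties will use the SEED Method and one county will use a modified Delphi method". The section presents this as a decision taken for comparative and logistical reasons, not as an allocation by chance.
- **Data analysis:** a two-level longitudinal model in which "variation in growth parameters among participants depending on the treatment status nested within location will be captured in the level 2 model". The same paragraph adds "If the ICC at the community level is negligible, the community will not be used in the nested structure", in which case robust standard errors are used.
- **Research questions:** SEED versus Delphi comes first, then intervention versus control.

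**The concern.** 'Group randomized' is a technical term. It tells the reader that intact groups were allocated, that variation between groups belongs in the error of the treatment effect, and that the number of groups limits the precision. A reader or an evidence synthesis that takes the Discussion at its word would look for cluster-randomised corrections in a trial that allocated people one by one.

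The Data analysis wording adds to the doubt. The trial has two treatment comparisons, and they stand in opposite relations to county: one lies within every county, the other lies entirely between counties. A single phrase that nests treatment status in location cannot describe both. In addition, the rule that drops community from the nested structure when the observed ICC is negligible lets the data decide on a term that the within-county randomisation already calls for.

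**Working it through.** **The plan's own figure.** The only figure attached to intervention versus control is the minimum detectable difference (MDD) of 0.12 for the total score (Table 4, n = 144, SD 0.37, alpha 0.05, power 80%). With 72 per arm and a two-sided test (sidedness is not stated), the plain formula gives (1.960 + 0.842) × 0.37 × √(2/72) = 0.173, so 0.12 is not reproduced. That gap is a separate matter and is not evidence for this point.

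**Step 1. What is randomised?** The Discussion says groups. The Abstract, Randomization, and Sample size and power analysis say participants. No section describes allocating a county or an intact group by chance. The label is contradicted by every passage that sets out the procedure.

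**Step 2. How does each factor lie across counties?** Planned numbers from Table 3:

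| | Site 1 | Site 2 | Site 3 | Total |
|---|---|---|---|---|
| Intervention | 24 | 24 | 24 | 72 |
| Control | 24 | 24 | 24 | 72 |
| Method in the intervention arm | SEED | SEED | Delphi | 48 SEED, 24 Delphi |

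All six arm-by-county cells are filled, so intervention versus control is crossed with county. Each county has one method only, so method is nested in county.

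**Step 3. What does this do to county variation?** Write c_j for the level of county j and d_j for its intervention effect.

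- *Intervention minus control in county j:* (c_j + d_j) − c_j = d_j, plus participant error. The county level cancels. With equal numbers, the overall contrast is the average of the three county differences. For a common effect its variance is 2 × SD² × (1 − ICC)/72. The documents give no ICC. At assumed values of 0, 0.01, 0.05 and 0.10, the MDD is 0.173, 0.172, 0.168 and 0.164. County variation does not widen this contrast. At a single time point, keeping three counties as a fixed factor uses 3 − 1 = 2 degrees of freedom, leaving 140 of 142.
- *SEED minus Delphi, intervention arms only:* the county part is (c_1 + c_2)/2 − c_3, with variance (1/4 + 1/4 + 1) = 1.5 times the between-county variance. More participants per county do not reduce it.
- *SEED minus Delphi, each set against its own controls:* the county levels cancel, leaving (d_1 + d_2)/2 − d_3. With one Delphi county, a difference between methods cannot be separated from anything else that makes the effect differ in that county.

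**Step 4. How can the model sentence be read?** It allows two readings:

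1. Treatment status is itself nested in location. Step 2 shows that this is false for intervention versus control and true for SEED versus Delphi.
2. Participants are nested in location, and treatment is a participant-level predictor at level 2. This is compatible with individual randomisation.

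The text does not settle which is meant.

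**The case against.** The strongest reply is that the label is one sentence in the Discussion and governs nothing. The sections that set the procedure agree with one another, and 'group' may be loose wording for an intervention delivered in groups. The inference is set by Data analysis, where the second reading in Step 4 is sound. An article also commonly leaves exact model terms to the analysis plan.

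Much of this stands. The label does not by itself determine the analysis, and nothing shows that the model sentence was written to follow it. The label is still a wrong statement of the design, and not merely an omitted detail. The ambiguity concerns the main randomised comparison.

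Three stronger readings are tempting and are not supported:

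- **The whole error structure is wrong.** A reader might take the six county-by-arm cells as the independent units. Under assumed ICCs of 0.01 to 0.05 that would inflate the standard error by 1.11 to 1.50. Even at ICC 0, a test on 4 degrees of freedom would cut power at a difference of 0.174 from 80% to 57%. The plan describes no such units and no such test, and those figures use one time point rather than the planned longitudinal model. They are not the size of this problem.
- **Literal nesting leaves no overall effect.** It does not: three county effects can be averaged.
- **Treatment is crossed with location, without qualification.** That would be wrong for SEED versus Delphi, the first research question.

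The objection is also right that relabelling leaves open how to handle clustering within SEED Topic groups, which meet separately. This point does not claim to resolve that.

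**Conclusion.** The concern holds in a limited form. The design label in the Discussion is wrong: participants are randomised individually, with a 1:1 target within each county, in sets of eight within a specific group. This follows from the article's own text and needs no assumption.

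The model wording in Data analysis is ambiguous. Read literally, it is wrong for intervention versus control and right for SEED versus Delphi, which is a non-randomised comparison of two counties with one. It does not show that the planned error structure as a whole is wrong, and no loss of power or precision can be attributed to it. What is at stake is a correct statement of the design, and a main contrast fixed in advance without depending on an observed ICC from three counties.

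**What to change.** **Discussion.** Replace the label with: 'individually randomized trial, stratified by county and stakeholder group, with group-delivered intervention arms'.

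**Data analysis.** Replace the phrase about treatment status and location with two statements:

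1. Intervention versus control is a participant-level, within-county contrast, with county kept as a fixed stratum whatever the observed community ICC.
2. SEED versus Delphi is a non-randomised comparison between counties (two versus one) and will be interpreted as such.

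The rule that removes community when its ICC is negligible should be amended to agree with the first statement.

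**Cost.** Wording edits in the protocol, carried into the analysis plan if there is one. No new participants, data or visits are needed. The fixed county term follows the strata already used for randomisation.

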### Methods and analysis

The aim of the proposed study is to increase the level of evidence for community-engaged research methods through a randomized controlled trial. The research objectives are to evaluate the effectiveness of the SEED Method and compare it to a modified Delphi method in opioid action planning projects in three rural Virginia communities.

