### Research questions

Are there differences in outcomes between engagement approaches (SEED and Delphi)?Are there differences between the intervention and control groups on the following key outcome variables?

Civic engagement (mobilization, motivation, and participation).Strategy development (the number, type, and diversity of strategies created).

The hypothesis is that higher levels of engagement will result in greater change in civic engagement and greater diversity in proposed strategies.

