As illustrated in Fig. 1, the study will take place in Virginia counties located in southwest and central Virginia. The counties have lower median household incomes and educational attainment, higher poverty rates, and higher levels of disability than the state average. Each community is struggling to deal with a growing opioid and substance use problem and is experiencing higher than average substance and opioid overdose deaths. Like many rural communities, they have limited healthcare services. Cooperative Extension has a presence within each county, implementing an evidence-based youth and family substance prevention program. As shown in Table 1, the counties differ in racial and ethnic composition. Counties 1 and 2 are about one-third Black and county 3 is 94% White. Although they had similar rates of emergency room visits for opioid overdoses in 2022, the opioid overdose death rate in 2023 was 24 per 100,000 in county 1, compared to 17 per 100,000 in counties 2 and 3. The Neonatal Abstinence Syndrome rate varied considerably across the counties.

**Table 1 Tab1:** County characteristics

	County 1	County 2	County 3
Population size 2022 (rounded)	34,000	22,000	30,000
Racial composition of the three largest population groups	White 60% Black 35% Multiracial 3%	White 61% Black 30% Multiracial 3%	White 94% Black 2% Multiracial 2%
Overdose ER visits 2022 (opioids only)	20 per 10,000	22 per 10,000	23 per 10,000
Overdose death rate 2023 (opioids only)	24 per 100,000	17 per 100,000	17 per 100,000
Neonatal Abstinence Syndrome cases per 1,000 births hospitalized	15 per 1,000	0 per 1,000	34 per 1,000

Sources: Population data: Data USA. (2022)

Opioid data: Virginia Department of Health. (2022). Emergency Department Visits. Retrieved from https://www.vdh.virginia.gov/drug-overdose-data/emergency-department/

Virginia Department of Health. (2023). Overdose Death Rates. Retrieved from https://www.vdh.virginia.gov/drug-overdose-data/overdose-deaths/

Virginia Department of Health. (2022). Neonatal Abstinence Syndrome (NAS). Retrieved from https://www.vdh.virginia.gov/drug-overdose-data/neonatal-abstinence-syndrome-nas/

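### The SEED-versus-Delphi comparison is not randomised and cannot be separated from county-specific effects, yet the Discussion says the design supports it and lists no such limitation

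*Protocol article*

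**What the plan says.** **Aim.** Methods and analysis: "The research objectives are to evaluate the effectiveness of the SEED Method and compare it to a modified Delphi method". Research questions opens with "Are there differences in outcomes between engagement approaches (SEED and Delphi". The Discussion concludes: "Given the design of the study, we will be able to compare the SEED Method to the Delphi Method". The same sentence goes on to say that both methods can be compared with control.

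**Assignment of method.** Interventions: "Two counties will use the SEED Method and one county will use a modified Delphi method". Funding was originally for SEED in all three counties, and the team then "decided to implement the Delphi method in one county for comparative and logistical reasons". No random assignment of county to method is described.

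**Randomisation.** Randomization: "participants will be randomized to an intervention or control group". The target is 24 per arm in each county (Recruitment; Table 3). Nobody can be allocated to SEED rather than Delphi.

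**Description and limitations.** The Discussion calls the study a group randomised trial. The limitations it names are sample size, a relatively new outcome scale, recruitment and retention, and decisions left to community teams. The coincidence of method with county is not among them.

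**The concern.** Method is constant within county and only one county uses Delphi. Whatever else is particular to that county therefore travels with the method. The protocol gives concrete reasons to expect differences:

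- Local teams decide group make-up, additional eligibility criteria and meeting mode (Participants).
- Stakeholders are identified with SEED matrices in the SEED counties and by consensus discussion in the Delphi county (Implementation).
- The counties differ in racial composition, opioid death rate and neonatal abstinence rate (Table 1).
- For the strategy outcome, the Delphi side is one group producing one set of strategies, so it has no replication.

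The Discussion offers the results to researchers and decision makers choosing between engagement methods. For that use, a reader needs to know that the between-method comparison lacks the protection of randomisation that the comparisons with control have.

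**Working it through.** **1. What the design identifies.** There are three counties and two arms, so six cell means. Let d1 and d2 be the intervention-minus-control effects in the SEED counties and d3 the effect in the Delphi county. Each d is a valid randomised estimate for its county. Write d1 = S + u1, d2 = S + u2 and d3 = D + u3, where S and D are the method effects and u is the part of the effect specific to that county, its team and its stakeholders.

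- *Direct contrast (intervention arms only).* Three county terms plus a method term make 4 columns of rank 3. Method cannot be separated from county.
- *Control-adjusted contrast.* (d1 + d2)/2 − d3 = (S − D) + (u1 + u2)/2 − u3. County differences in outcome level cancel, but the u terms do not. County, treatment and treatment-by-method make 5 columns of rank 5, so the contrast is estimable if all u are taken as zero. Adding county-by-treatment terms gives 7 columns of rank 6, and the method effect is then aliased.

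The SEED counties give one degree of freedom for between-county variation in effect (d1 against d2), and Delphi gives none. More participants, covariates or a random effect over three counties cannot change this.

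**2. The plan's own figure.** Table 4 gives a minimum detectable difference (MDD) of 0.12 (6.5%) for the total score, with SD 0.37 and mean 1.87. The text gives alpha 0.05 and beta 0.20; two-sided testing is assumed here. MDD = (1.960 + 0.842) × SD × √(sum of 1/n).

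- 72 against 72: 2.802 × 0.37 × √(2/72) = 0.173, not 0.12.
- 144 against 144: 2.802 × 0.37 × √(2/144) = 0.122, which is 6.5% of 1.87.

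The printed figure is therefore not reproduced at the planned arm sizes. That is a separate problem, and this point does not rest on it.

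**3. Same formula for the contrasts at issue** (single-time SD, no clustering, no baseline adjustment):

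| Contrast | √(sum of 1/n) | MDD |
|---|---|---|
| SEED vs control, 48/48 | √(2/48) = 0.204 | 0.21 |
| Delphi vs control, 24/24 | √(2/24) = 0.289 | 0.30 |
| SEED vs Delphi, direct, 48/24 | √(1/48 + 1/24) = 0.250 | 0.26 |
| SEED vs Delphi, control-adjusted | √(2/48 + 2/24) = 0.354 | 0.37 |

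Like for like, 0.366/0.173 is about 2.1.

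**4. What ignoring county variation does.** Suppose the methods do not differ and the county terms have SD τ. The protocol gives no value for τ, so a range is assumed. The contrast then gains variance τ²(1 + 1/2), from one Delphi county against the mean of two SEED counties. A nominal 5% test that ignores this rejects as follows:

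| τ | Direct (county levels vary) | Control-adjusted (county effects vary) |
|---|---|---|
| 0 | 5% | 5% |
| 0.05 | 10% | 8% |
| 0.10 | 24% | 15% |
| 0.15 | 38% | 26% |
| 0.20 | 49% | 36% |

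**The case against.** The best defence is that every county has its own concurrent randomised controls. That stands in part. Intervention versus control within county is a sound randomised comparison, and the half of the Discussion sentence about comparing each method with control is correct. The controls also remove county differences in outcome level, so a reader who infers that no SEED-Delphi contrast can be formed would go too far. What remains aliased is variation in the treatment effect between counties.

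Other strong readings are not supported:

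- *That the trial will present the method comparison as randomised evidence, or will pool SEED and Delphi.* Data analysis names neither a direct arm contrast nor a pooled one. The protocol states openly what is randomised and how Delphi entered. Its praise of a rigorous randomised design describes the trial as a whole.
- *That the adjusted MDD is three times the planned one.* Table 4 does not say which contrast 0.12 refers to, and the formula does not return 0.12 at 72 per arm.
- *That the Delphi county is the one with a different population.* The text says "Counties 1 and 2 are about one-third Black and county 3 is 94% White", but nothing visible equates Site 3 in Table 3 with County 3 in Table 1. This is likely, but the argument does not need it.

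The MDDs above also do not model the planned longitudinal analysis of change. With an assumed baseline correlation of 0.5 to 0.7, the factor √(1 − r²) would take 0.366 to about 0.32 to 0.26. Clustering would push the other way.

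**Conclusion.** The point holds in this form. The protocol presents the SEED-Delphi comparison as something the design delivers, but that comparison is non-randomised. Taken directly, it is confounded with county, team and stakeholder selection. Adjusted for own-county controls, it is still aliased with county-specific treatment effects, with two SEED counties against one Delphi county. The Discussion omits this from its limitations and calls the study group randomised although individuals are randomised. This conclusion follows from the allocation alone and needs no numerical assumption.

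The sizes are illustrative: MDDs of about 0.21, 0.30 and 0.37 for SEED versus control, Delphi versus control and the adjusted contrast, the last about twice the 0.17 for 72 against 72. They assume SD 0.37, a single-time outcome, two-sided alpha 0.05, 80% power and no clustering or baseline adjustment. The error rates depend on an assumed τ. The within-county randomised comparisons with control are not affected.

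**What to change.** 1. Report SEED versus control (Sites 1 and 2) and Delphi versus control (Site 3) as the randomised comparisons.
2. Define any SEED-Delphi comparison as the difference of these within-county effects (arm-by-method interaction), and label it non-randomised and exploratory in the objective, the research question and the results.
3. Qualify the Discussion sentence rather than delete it. The statement that each method can be compared with control should stay.
4. Correct the group-randomised description to individual randomisation within county.
5. Add to the limitations that method coincides with county, that Delphi has one county, and that method was not randomly assigned.

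The cost is some rewording and one interaction term. Recruitment, randomisation and data collection do not change. The real price is a weaker claim for the method comparison.

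### The rule that drops county from the model when its ICC is negligible can let controls from other counties into the SEED and Delphi effects

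*Protocol article*

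**What the plan says.** **Design.** Under Interventions, "Two counties will use the SEED Method and one county will use a modified Delphi method". The investigators had been funded for SEED in all three counties and "decided to implement the Delphi method in one county for comparative and logistical reasons"; nothing suggests that method was assigned to county at random. Under Randomization, people are taken in sets of eight from a given stakeholder group, and "participants will be randomized to an intervention or control group". Table 3 plans 24 intervention and 24 control participants at every site. Implementation describes a separate control group in each county.

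**Analysis.** The two-level growth model in Data analysis places treatment status within location at level 2. Before that comes a conditional step: "If the ICC at the community level is negligible, the community will not be used in the nested structure", with robust standard errors estimated instead. No cut-off for negligible is given, and the SEED-control and Delphi-control contrasts are not written out.

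**Discussion.** The authors state that the design lets them set SEED against Delphi and "compare both of these methods to the control group", with control group in the singular. The same paragraph says "This protocol describes a group randomized controlled trial".

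**The concern.** County plays two parts in this trial. It is a stratum within which individuals are randomised, and it wholly determines which method a person could receive. Nobody in a SEED county could have been allocated to Delphi, or the reverse. The randomised comparators are therefore the 48 controls of the two SEED counties for SEED, and the 24 controls of the third county for Delphi.

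A rule that removes such a stratum on the strength of an estimated ICC treats county as a question of variance only. If county leaves the model and the methods are coded as SEED, Delphi and control, the reference becomes all 72 controls. SEED then borrows 24 non-randomised controls and Delphi borrows 48. The method-control effects are the only randomised evidence on each method, and they would become partly between-county comparisons. Their biases have opposite signs, so a difference between the methods could appear where none exists.

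**Working it through.** **Inputs.** Table 3: 24 v 24 in each of three counties. Table 4: SD 0.37 for the Mobilization Scale total, stated minimum detectable difference 0.12. Alpha 0.05, taken as two-sided. The documents give no figure for county differences in change, so d is assumed throughout.

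**The plan's own figure.** For 72 v 72, (1.96 + 0.84) × 0.37 × √(2/72) = 0.173, not 0.12. The stated value follows from (1.96 + 0.84) × 0.37 × √(1/72) = 0.122. That discrepancy is a separate matter. Here 0.12 serves only as a yardstick for d.

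**Bias under pooled controls.** Let c1, c2 (SEED counties) and c3 (Delphi county) be the mean changes without intervention, and d = c3 - (c1 + c2)/2. The pooled control mean is (c1 + c2 + c3)/3.

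- Delphi: c3 - (c1 + c2 + c3)/3 = +2d/3
- SEED: (c1 + c2)/2 - (c1 + c2 + c3)/3 = -d/3
- SEED effect minus Delphi effect: -d/3 - 2d/3 = -d
- All intervention v all control: (c1 + c2 + c3)/3 - (c1 + c2 + c3)/3 = 0

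**Standard errors (SD 0.37).**

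| Contrast | Pooled controls | Own-county controls |
|---|---|---|
| Delphi | 0.37√(1/24 + 1/72) = 0.087 | 0.37√(2/24) = 0.107 |
| SEED | 0.37√(1/48 + 1/72) = 0.069 | 0.37√(2/48) = 0.076 |

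**Type I error if pooled**, from Φ(-1.96 + b/SE) + Φ(-1.96 - b/SE), where b is the bias:

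| Assumed d | Delphi bias | Delphi type I | SEED bias | SEED type I |
|---|---|---|---|---|
| 0.05 | +0.033 | 6.7% | -0.017 | 5.7% |
| 0.10 | +0.067 | 11.9% | -0.033 | 7.7% |
| 0.12 | +0.080 | 15.1% | -0.040 | 8.9% |
| 0.20 | +0.133 | 33.3% | -0.067 | 16.2% |

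Simulation with no true effect agrees. At d = 0.20 the pooled estimates averaged +0.131 (Delphi) and -0.064 (SEED), with rejection rates of 30.1% and 14.7%. With county terms in the model both averaged about zero and rejection was about 5%.

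**Does the ICC step guard against this?** Suppose negligible meant a non-significant F-test for county (an assumption, since no rule is stated). At d = 0.12 the test has about 35% power, so county would be dropped in about 65% of trials. In those trials alone the mean bias is about +0.06 (Delphi) and -0.03 (SEED), with rejection of about 8% to 9% and 6%. The step lessens the harm but does not remove it.

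**The case against.** A reader might infer from the Discussion that a pooled-control comparison is the planned analysis. The documents do not support that. The singular control group occurs in a sentence about what the design permits and can be read as the control condition. Implementation describes separate county control groups, Table 3 lists controls by site, and the default model sets treatment within location, which points to within-county comparison. Pooling needs two events together: the ICC step removes community, and the methods are then coded against all controls. The second is not written anywhere, and the coding of contrasts is detail that an article may leave to a fuller document. Covariates are also allowed at both levels, so county could return that way.

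The size is assumed too. The outcome is change, so the county differences in Table 1 do not by themselves imply any d. County means of 0, 0 and 0.12 with SD 0.37 correspond to an ICC of about 0.03, which an analyst might not call negligible; community would then stay in.

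A reader might also extend the point to the strategy lists, since the Discussion will "compare the number and types of strategies created and prioritized using the three methods evaluated". Implementation gives one control list per county and no pooling of lists is described, so that extension does not hold.

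All of this limits the severity. What remains is that the ICC step is a stated rule, not a silence. It is data-driven, has no threshold, rests on three counties and removes a randomisation stratum. Its substitute, robust standard errors, acts on variance and leaves bias in place.

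**Conclusion.** The concern holds in conditional form. The default model is sound on this point, and the overall intervention-control contrast is not biased by omitting county at the planned 1:1 numbers. The fault is the rule that allows county to be dropped, together with Discussion wording that does not tie each method to its own counties' controls. If both lead to pooling, the Delphi effect is biased by +2d/3 and the SEED effect by -d/3. Type I error is then about 7% and 6% at d = 0.05, and about 15% and 9% at d = 0.12. These figures assume SD 0.37, the planned numbers, that pooling takes place and the chosen d, for which the documents offer no estimate.

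The label group randomised contradicts the Randomization section and is a separate wording error; it is not evidence of pooling. This should be fixed but is not critical: the harm is conditional and of unknown size, while the repair is almost free.

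**What to change.** 1. In Data analysis, keep county as a fixed term whatever the ICC, crossed with arm for the method effects. The ICC may still be reported but should not decide whether county stays.
2. Define the method effects there: SEED participants v controls of the two SEED counties (48 v 48), and Delphi participants v controls of the Delphi county (24 v 24).
3. In the Discussion, say that each method is compared with the controls of its own county or counties.
4. In the Discussion, replace the group-randomised label with individual randomisation within county and stakeholder group.

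**Cost.** A few sentences and one model term. Compared with pooled controls, standard errors rise from about 0.087 to 0.107 for Delphi and from 0.069 to 0.076 for SEED. In detectable differences (two-sided 0.05, 80% power, no ICC inflation) that is 0.24 to 0.30 and 0.19 to 0.21. The precision given up came from non-randomised controls.

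**What it does not solve.** SEED v Delphi remains a non-randomised comparison between counties, because Delphi is used in only one, and should be described as such.
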